##### First Visit (Baseline Measurements)

3.7.5.1

At the first visit, baseline characteristics such as sociodemographic characteristics, phenotypic taste sensitivity, and physical activity will be measured. Food preferences will be measured using a validated Food Liking Questionnaire (FLQ), and dietary quality will be measured using the validated Australian Recommended Food Score (ARFS). Energy intake will be assessed using 3‐day food records supplemented with 24 h dietary recalls. To minimize errors in portion size estimation, participants will be instructed in the use of standardized and household measures. During the 24 h recall, participants will provide a detailed account of all foods and beverages consumed the preceding day, including brand names, ingredients, condiments, cooking methods, and portion sizes. Following the initial recall, the data collector (principal investigator) will probe for any omitted items, clarify portion sizes, and review the record jointly with the participant to ensure accuracy, with modifications made as required.

At the same visit, participants will be provided with a 3‐day food record sheet and instructed to record their intake over three non‐consecutive days (two weekdays and one weekend) during the following week. To improve accuracy, they will be encouraged to record portion sizes using package information or standardized measures and, when these are not feasible, to rely on household measures. Participants will also be advised to complete the record as soon as possible after each eating occasion to minimize underreporting and improve portion size estimations. The completed records will be reviewed by the researcher at the next visit for completeness and accuracy.

Furthermore, anthropometry and body composition will be measured as secondary outcomes of interest. During this initial visit, participants will be asked to provide their preferred way of contact (phone, email, or social media) and postal address (suburb, street, and postal code) for follow‐up purposes.

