### Project Phases and Study Design

3.1

Each phase of the project will use different quasi‐experimental designs. Table 1 presents a summary of the study design, population, setting, variables, sample size, and study period for each phase.

**TABLE 1 fsn371640-tbl-0001:** Study designs, study populations, study settings, study variables, sample size and estimated study periods for each phase of the project.

	Project phases			
	Phase 1	Phase 2	Phase 3	Phase 4
Study design	Three‐arm pre‐post parallel design	Four‐arm placebo‐controlled single‐blind pre‐post parallel design	Four‐arm placebo‐controlled single‐blind pre‐post parallel design	Two‐arm placebo‐controlled, single‐blind (participants), parallel feasibility trial
Study population	Healthy‐weight adults living in Australia	Healthy‐weight adults living in Australia	Overweight or Obese adults living in Australia	Overweight or Obese adults living in Australia
Study setting	Laboratory‐based	Laboratory‐based	Laboratory‐based	In a natural environment (at home)
Independent variable	Different MB doses (175, 350, and 700 mg)	Different MB doses (175, 350, and 700 mg) and placebo	Different MB doses (175, 350, and 700 mg) and placebo	MB or Placebo consumption in a natural environment
Dependent variable	Sour, bitter, tart, and sweet taste perception ratings of food‐based solutions and individual food items	Ratings for sourness and bitterness taste perceptions, overall liking and intake of hypo‐palatable mixed vegetarian salad Ratings for sweetness taste perceptions and overall liking of SSBs	As mentioned in Phase 2	Primary outcomes Food preferences (Overall meal liking and preferences across time) Energy intake Dietary quality Other outcomes of interest Feasibility of the treatment protocol and study procedures Appetite Anthropometry/Body composition
Sample size	54	40	40	30
Proposed study period	1 July–30 September, 2024	1 November 2024–30 September 2025	1 December–30 June, 2025	1 May–30 December, 2025

*Note:* Sociodemographic characteristics (sex*, age, income, employment status, and education status), phenotypic taste perception, genotypic taste sensitivity, mouth pH, anthropometry, and body composition will be collected as covariates. In Phases 3 and 4, comorbidities (e.g., diabetes, hypertension) and medication use (self‐reported) will also be assessed. In Phase 4, physical activity will be measured as a covariate for secondary outcomes. *Sex is classified based on biological characteristics.

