
**FIGURE 2 fsn371640-fig-0002:**
[figure not shown]
Phases 2 and three study design.

#### Phase 3

3.7.4

The study design and data collection procedures followed in this phase are identical to those used in Phase 2 (Figure 2). They vary among study participants (Phase 2 is on healthy‐weight adults, and Phase 3 is on overweight or obese adults). A separate investigation is required because taste sensitivity alters with overweight and obesity (Harnischfeger and Dando 2021; Rohde et al. 2020; Vignini et al. 2019). Therefore, the dose of MB required to induce a change in taste perception and food liking may be different for overweight and obese adults than for healthy‐weight adults.

#### Phase 4

3.7.5

This will be a two‐arm, placebo‐controlled, single‐blind, parallel feasibility trial conducted over a 12‐week follow‐up period, in which participants will be blinded to group allocation. Blinding of participants will be maintained via the use of MB and Placebo tablets of similar size and closely matched colourings. Most importantly, participants will only receive their allocated treatment tablets and will not be privy to viewing the alternative treatment tablet. To minimize the risk of unblinding within households, only one participant per household will be enrolled. As this is a feasibility study, the success of blinding will also be evaluated by asking participants at the end of the trial whether they believed they had received MB or placebo.

The participants will have four visits to the Gold Coast campus, or they will be visited at their home by the principal investigator, based on their preference. That is, a first visit (at baseline), a second visit (at the end of the baseline week), a third visit (at the end of the 6th week), and a fourth visit (at the end of the 12th week). The main outcomes of interest are food preferences, energy intake, and dietary quality. Additionally, it will explore its effect on the overall liking of mixed meals (breakfast, lunch, dinner, and snacks) and on appetite. As it is a feasibility study, the other main outcomes of interest will be exploring the feasibility indicators (recruitment, blinding, allocation, retention, compliance, and adverse effects). Furthermore, as a secondary outcome, the study will investigate the effect of MB on anthropometry and body composition. Table 5 indicates the details of the study variables to be measured, including their frequency and the study visits at which they will be assessed.

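### Phase 4 names no blinded interviewer for the week 6 and week 12 dietary recalls, so part of the energy-intake data is open to arm-dependent elicitation

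*Protocol article*

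**What the plan says.** **Blinding.** Table 1 (section 3.1) describes Phase 4 as a "single‐blind (participants), parallel feasibility trial". Section 3.7.5 agrees: it is a trial "in which participants will be blinded to group allocation", and it mentions no blinding of the investigator, interviewer or analyst. The means are "MB and Placebo tablets of similar size and closely matched colourings", and the text adds that "participants will only receive their allocated treatment tablets and will not be privy to viewing the alternative treatment tablet".

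**Outcome.** Table 1 lists energy intake as a primary outcome beside food preferences and dietary quality. Table 3 measures it by a 3-day food record, supplemented by two 24-h recalls (one weekday, one weekend day) at each of baseline, week 6 and week 12.

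**Who collects it.** Section 3.7.5.1, on the first visit, says that "the data collector (principal investigator) will probe for any omitted items, clarify portion sizes, and review the record jointly with the participant", and that changes are made where needed. On the 3-day records it says: "The completed records will be reviewed by the researcher at the next visit for completeness and accuracy". Section 3.7.5 says participants attend the campus or "they will be visited at their home by the principal investigator, based on their preference".

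**Order of events.** Allocation takes place at the second visit (section 3.7.5.2). The recall is repeated at the third and fourth visits (sections 3.7.5.3 and 3.7.5.4).

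**Stated limitations.** The Comments (section 4) count researcher probing among the remedies for self-report bias. They do not mention that probing could differ between arms.

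**The concern.** A placebo controls what participants expect and report. It does not control what an interviewer draws out of them. If the interviewer knows the arm, slightly more persistent probing for forgotten snacks in one arm, or slightly different portion estimates, produces a between-arm difference in energy intake without any true effect. Randomisation and participant blinding do not remove it, and a mixed model cannot separate it from a treatment effect.

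The main harm in a 30-person feasibility trial is to the estimate carried forward: the Comments make larger studies depend on promising effects here. Energy intake is the outcome most exposed. Dietary quality could also be touched, because Table 3 derives diet-quality indices from the recalled foods in addition to the participant-completed ARFS questionnaire.

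**Working it through.** No figure in the protocol states or depends on interviewer blinding, so there is none to reproduce. The check has two parts.

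**1. The text set side by side**

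| Step | Timing | Who, as stated | Can it differ by arm? |
|---|---|---|---|
| Baseline 24-h recall, probed and modified (3.7.5.1) | Before allocation | Principal investigator | No |
| Review of the baseline 3-day record (3.7.5.1) | Second visit; record collected, then allocation (3.7.5.2) | The researcher | No |
| Week 6 recall and record (3.7.5.3) | After allocation | Not restated | Yes, if the interviewer knows the arm |
| Week 12 recall and record (3.7.5.4) | After allocation | Not restated | Yes, if the interviewer knows the arm |

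Two inferences are needed. First, the principal investigator, named as data collector at baseline and as home visitor, also interviews at weeks 6 and 12. Second, this person knows the allocation, because blinding is expressly limited to participants. Both are the natural reading; neither is stated outright.

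**2. Scale, as an illustration only**

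From the documents: the Introduction cites a reduction of about 441 kJ with miracle berry (MB) against placebo in an earlier crossover trial with provided meals; each time point has three record days and two recall days (Table 3). Assumed: extra probing finds one item of 400-600 kJ in half of one arm's recalls and none in the other arm's.

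- Shift in that arm's recall mean: 0.5 × 400 = 200 kJ to 0.5 × 600 = 300 kJ.
- If recalls alone defined energy intake: 200/441 = 45% to 300/441 = 68% of the cited effect.
- The protocol gives no rule for combining the two instruments. If all five days count equally and the records are unaffected: 200 × 2/5 = 80 kJ to 300 × 2/5 = 120 kJ, that is 80/441 = 18% to 120/441 = 27%.

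In standard deviation (SD) units, because the protocol gives no SD for energy intake: for a differential shift of b SD with no true effect and n per arm, the chance of a two-sided 5% rejection is Φ(b/√(2/n) − 1.96) + Φ(−b/√(2/n) − 1.96).

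| Shift b (SD, assumed) | n = 15 per arm | n = 10 per arm |
|---|---|---|
| 0 | 5.0% | 5.0% |
| 0.1 | 5.9% | 5.6% |
| 0.2 | 8.5% | 7.3% |
| 0.3 | 13.0% | 10.3% |
| 0.5 | 27.8% | 20.1% |

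Fifteen per arm is the recruitment target and ten the stated minimum (section 3.4.3).

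**The case against.** The strongest reply is that the protocol shows less than it seems to.

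- **Both described procedures precede allocation.** The probed recall and the record review in section 3.7.5.1 concern baseline data and cannot differ by arm. This stands. The concern applies only to weeks 6 and 12, by inference from the same data-collector role.
- **Knowledge of the arm is not stated.** Nobody is named as holding the allocation list, and details of how blinding and allocation are assessed are in Table S5, which is not shown. This also stands. But an express limit of blinding to participants gives no reason to assume a blinded interviewer.
- **There are safeguards.** Table 3 calls the interviews structured and prescribes portion-size aids, and the review is joint with a blinded participant. These limit discretion without removing it, since open probing and modification remain.
- **The size is assumed.** This is correct. A reader might infer that one extra item in every recall would match or exceed the cited effect. At 400 kJ it would not (400/441 = 91%), and the recalls only supplement the records. The 441 kJ also comes from controlled meals, which the Introduction itself says limits generalisability.
- **The tablets may not permit investigator blinding.** They are similar and closely matched, not identical, and participants' blinding relies also on never seeing the other tablet. Someone handling both kinds might tell them apart. The principal investigator also monitors daily responses on perceived change in liking (section 3.7.5.5.1), which may hint at the arm. This stands and shapes the remedy.
- **The consequence is limited.** The trial is a small feasibility study, the food-liking and ARFS measures are questionnaires, and the Comments already advise caution with self-reported diet. That caution does not cover interviewer bias.

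**Conclusion.** The concern holds in a limited form. Phase 4 blinds participants only, the one named data collector probes and may modify the recall, the recall is repeated twice after allocation, and no blinded interviewer is named. Part of the data for a primary outcome is therefore open to elicitation that depends on the arm, and the stated limitations do not say so.

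A reader might go further and conclude that the protocol has an investigator known to be unblinded editing post-allocation recalls, or that the matched tablets would by themselves blind that person. The text supports neither.

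The magnitude is unknown. The 80-120 kJ illustration (18-27% of 441 kJ) rests on the assumed item size and frequency, no equivalent probing in the other arm, equal weighting of five days, and unaffected food records. It shows that modest differential probing would not be negligible; it does not estimate the bias. The change is worth making because it is cheap and protects the estimate that would inform a larger trial.

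**What to change.** 1. Have the donor, or a colleague not involved in data collection, pack the MB and placebo tablets in opaque, sealed containers numbered by participant, and hold the code until the dietary data are locked. The principal investigator then dispenses by number without seeing the tablets, and does the week 6 and week 12 recalls and record reviews without knowing the arm. Amend the blinding description in Table 1 and section 3.7.5 accordingly.
2. Use the same fixed probe script in both arms, building on the structured interview in Table 3.
3. Keep the participant's unedited entries beside any modified value, so that edits can be compared by arm.
4. Record the principal investigator's guess of allocation, alongside the participants' guess already planned at the end of the trial. State any remaining unblinding as a limitation in the Comments.

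The cost is a one-off packing and coding task for 30 participants and a code-break procedure, with no extra visit or assessor. Blinding may still be imperfect for the reasons given above. If coded packs prove impractical, or Phase 4 is already under way, items 2 and 3 and a declared limitation remain possible.

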##### Second Visit (End of Baseline Week)

3.7.5.2

In this visit, the 3‐day food record sheet provided in the first visit will be collected from study participants. Then, participants (*n* = 30) will be allocated into two arms. Then, participants will be given the required number of tablets (MB or placebo) in their respective groups for 6 weeks. Moreover, they will be provided with a 3‐day food record sheet and requested to complete it in the last week of this follow‐up period, before the third. Instructions will be provided to encourage participants to use a minimum amount of lime or lime juice while they administer tablets (to activate miraculin) with their meals in their daily lives. However, unlike the lab phases, no other strict standardization procedures will be imposed, as the aim is to evaluate the feasibility and acceptability of MB use in everyday dietary contexts.

##### Third Visit (End of the 6th Week)

3.7.5.3

During this visit, the 3‐day food record sheet, the adverse effect recording sheet, and the daily follow‐up questionnaire provided at the second visit will also be collected. Then, all outcomes of interest measured at the baseline (FLQ, ARFS questionnaires, 24‐h dietary recall, anthropometry and body composition measurement) and physical activity as a covariate will be measured. Participants in their respective groups will receive the required MB or placebo tablets for the next 6 weeks. Additionally, to measure their energy intake, they will receive the 3‐day food record sheet and be instructed to complete it in the next sixth week (at 12 weeks of intervention).

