##### Fourth Visit (End of the 12th Week)

3.7.5.4

On this visit, all measurements taken at the third visit will be measured, and the 3‐day food record sheet provided on the third visit will be collected.

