4	To measure the feasibility of the treatment protocol, study procedures and outcome	Treatment ○ MB ○ Placebo Follow‐up duration	Retention rate, Compliance rate, adverse effects, recruitment and allocation success rate	Frequency and descriptive explanations	Descriptive statistics ○ Mean (±SD) for normally distributed data, otherwise Median (±IQR) ○ Counts and frequencies
	To measure the effect of MB consumption on food preferences in overweight or obese adults living in their natural environment (i.e., at home).	Treatment ○ MB ○ Placebo Measurement time (baseline, mid‐protocol, completion)	Changes in food preferences	FLQ as a continuous scale (Food liking score) on three occasions (at baseline, week 6, week 12, and at the end line)	Descriptive statistics ○ Mean (+SD) for normally distributed data, otherwise Median (+IQR) ○ Counts and frequencies The treatment effect will be assessed using LMM or GLMM, as proposed in Phase 1. Given that this is a feasibility trial, a sensitivity power analysis will be conducted to determine the minimum detectable effect size based on the available sample size and the desired statistical power. The analysis will be conducted on an intention‐to‐treat basis
	To investigate the effect of MB consumption on the energy intake of overweight or obese adults living in their natural environment (i.e., at home)	Treatment ○ MB or ○ Placebo Measurement time (baseline, mid‐protocol, completion)	Changes in energy intake	Diet intake converted to kilo calories (at baseline, week 6, week 12)	
	To determine the effect of MB consumption on the diet quality of overweight or obese adults living in their natural environment (i.e., at home)	Treatment ○ MB or ○ Placebo Measurement time (baseline, mid‐protocol, completion)	Changes in diet quality score	Total ARFS score and each food group ARFS score (at baseline, week six, week 12)	
	To determine the effect of MB consumption on overall liking of mixed meals served as breakfast, lunch, dinner, and snacks in overweight or obese adults living in their natural environment (i.e., at home)	Treatment ○ MB or ○ Placebo Measurement time (daily throughout the follow‐up period)	Comparing the change in overall liking of the meal (served as breakfast, lunch, dinner, snack)	gLMS measured daily from week 2 to week 12 (0–100) Proportion (self‐reported yes/no)	

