	To determine the effect of MB consumption on the appetite for different foods in overweight or obese adults living in their natural environment (i.e., at home)	Treatment ○ MB or ○ Placebo Measurement time (daily throughout the follow‐up period)	Comparing the change in appetite	Proportion (self‐reported yes/no)	
To measure the effect of MB consumption on anthropometric and body composition measurements of overweight or obese adults living in their natural environment (i.e., at home)	Treatment ○ MB or ○ Placebo Measurement time (baseline, mid‐protocol, completion)	Changes in anthropometric and body composition measures	Weight, BMI, WC, WHtR, FFM, Body Fat Percentage, Body water (at baseline, week 6, week 12)		

Abbreviations: FFM, fat‐free mass; FM, fat mass; WC, waist circumference; WHtR, Waist‐to‐height ratio.

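### Phase 4 re-measures physical activity after tablets start, expressly as a covariate for the body-measure outcomes, and no rule limits adjustment to values recorded before allocation

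*Protocol article*

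**What the plan says.** All references are to the Protocol article.

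- **Baseline (3.7.5.1).** At visit 1, "baseline characteristics such as sociodemographic characteristics, phenotypic taste sensitivity, and physical activity will be measured". Anthropometry and body composition are also taken then, as secondary outcomes.
- **Allocation (3.7.5.2).** Participants are allocated, and receive their first six weeks of tablets, at visit 2.
- **Week 6 (3.7.5.3).** The baseline outcomes are measured again, "and physical activity as a covariate will be measured".
- **Week 12 (3.7.5.4).** Here "all measurements taken at the third visit will be measured", so by the text activity is recorded a third time.
- **Scope (Table 1 note).** "In Phase 4, physical activity will be measured as a covariate for secondary outcomes". Section 3.7.5 identifies the secondary outcomes as anthropometry and body composition.
- **Body measures as covariates (Table 1 note).** The project-wide list says "mouth pH, anthropometry, and body composition will be collected as covariates", with no time point and no Phase 4 exception.
- **Body measures as outcomes (Table 6).** A Phase 4 dependent variable is "Changes in anthropometric and body composition measures".
- **Model (Table 6).** Phase 4 takes over the Phase 1 mixed model: treatment, time, a random participant effect, and further covariates where they improve fit. Age, sex and taste sensitivity are the examples, and AIC decides what is kept. For Phase 4, "The analysis will be conducted on an intention‐to‐treat basis".

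**The concern.** A covariate recorded before allocation cannot be a consequence of treatment, so adjusting for it leaves the treatment effect intact and may sharpen it. A covariate recorded after six or twelve weeks of tablets can be such a consequence. MB might alter activity directly, or alter weight and thereby activity. The model coefficient would then no longer be the total effect of being allocated MB. It would be a conditional contrast, which also carries bias if activity and body measures share an unmeasured cause.

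The protocol gives the week 6 activity value no role other than covariate. Table 3 says the IPAQ covers the previous 7 days, so at week 6 its recall window lies wholly after tablets began. AIC does not guard against this, because it rewards variables that track the concurrent outcome whether or not treatment moved them. At stake is the reading of the Phase 4 results on weight, waist and body composition.

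**Working it through.** **The plan's own figure.** The Phase 4 size is not in dispute and only sets the scale. A minimum of 20 with 32% attrition gives 20 / (1 − 0.32) = 29.4, rounded up to 30. Per arm, 10 / 0.68 = 14.7, rounded up to 15. Both match section 3.4.3.

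**Order of events.** Activity is recorded at visit 1, allocation and tablets come at visit 2, and activity is recorded again at week 6 (as a covariate) and week 12 (through 3.7.5.4). The first value precedes treatment and the other two follow it. Nothing in Table 1, 3.7.5.3 or Table 6 says which of them enters the model.

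**What follow-up adjustment would do.** The documents give no effect of MB on activity, so every input here is an assumption:

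- 15 per arm, true total effect on the outcome 0.5 units, residual SD 0.9;
- MB shifts follow-up activity by a = 0, 0.25, 0.5 or 0.8 units;
- the outcome changes by b = 0.2 or 0.4 per unit of activity;
- an unmeasured common cause acts on both activity and outcome with strength u = 0 or 0.4;
- follow-up activity has within-arm variance 0.25 + u² + (0.75 − u²) = 1.

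Given arm, the slope of the outcome on follow-up activity is b + u². The coefficient adjusted for follow-up activity is therefore

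adjusted effect = 0.5 − a × (b + u²).

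For example, a = 0.5, b = 0.4, u = 0.4 gives 0.5 − 0.5 × 0.56 = 0.22. Each cell shows the formula, then the mean of 4,000 simulated trials:

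| a | b = 0.2, u = 0 | b = 0.2, u = 0.4 | b = 0.4, u = 0 | b = 0.4, u = 0.4 |
|---|---|---|---|---|
| 0 | 0.50 / 0.501 | 0.50 / 0.506 | 0.50 / 0.504 | 0.50 / 0.490 |
| 0.25 | 0.45 / 0.445 | 0.41 / 0.419 | 0.40 / 0.388 | 0.36 / 0.361 |
| 0.5 | 0.40 / 0.409 | 0.32 / 0.317 | 0.30 / 0.310 | 0.22 / 0.222 |
| 0.8 | 0.34 / 0.338 | 0.21 / 0.219 | 0.18 / 0.184 | 0.05 / 0.047 |

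Adjusting for baseline activity instead gave 0.486 to 0.515 in all sixteen settings.

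**Direction.** The sign is not fixed. With a = −0.5, b = 0.4 and u = 0, the formula gives 0.5 + 0.20 = 0.70, away from zero.

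**The route through weight.** If activity responds linearly to weight with within-arm correlation r, and nothing else links them, the adjusted effect is the true effect × (1 − r²). An effect of 0.5 becomes 0.48 at r = 0.2 and 0.42 at r = 0.4.

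**The case against.** The strongest reply is that the protocol never says a follow-up value enters a model. Table 6 names age, sex and taste sensitivity, all fixed before treatment. Visit 1 values of activity and body measures exist, and adjusting for those is legitimate. Which time point a covariate takes is often left to an analysis plan, and this is a condensed article. The outcomes concerned are secondary ones in a 30-person feasibility trial.

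Much of that stands, and it rules out several stronger readings that a reader might infer:

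- *That the models will adjust away part of any MB effect.* The text labels the follow-up value a covariate but does not state its use, and without an effect of MB on activity there is no such bias.
- *That energy intake, food preferences or dietary quality are affected.* The Table 1 note confines activity to secondary outcomes, and no section proposes adjusting energy intake for concurrent weight.
- *That week 6 or week 12 body measures enter a Phase 4 model.* The Table 1 note covers all four phases. In Phases 1 to 3 these measures precede any tablet, and in Phase 4 the visit 1 values satisfy the note. It merely fails to except the later ones.
- *That the intention-to-treat comparison is broken.* Adjustment moves nobody out of the allocated arm. It changes what is estimated.

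What does not stand is that this is only silence. Section 3.7.5.3 assigns the week 6 measurement a covariate role, a baseline-only adjustment would not need that measurement, and the stated selection rule lets it in.

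**Conclusion.** The point holds in a limited form. The protocol designates physical activity measured after tablets start as a covariate for the Phase 4 body-measure outcomes, and its fit-driven selection rule does not exclude it. A model that used it would estimate the total effect of allocation to MB only if MB leaves activity unchanged. Otherwise the estimate may be biased, in a direction and by an amount that the documents do not fix.

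The illustration runs from no bias (0.49 to 0.51 against a true 0.5) to near loss of the effect (0.05) under the strongest assumed shift and common cause. These values show the mechanism and do not forecast this trial. They assume linear effects and allocation unrelated to baseline activity.

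The double listing of body measures, as covariates in the Table 1 note and as Phase 4 outcomes, is a lesser ambiguity of the same kind. The week 12 statement rests on the text of 3.7.5.4 and not on the marks in Table 5.

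**What to change.** - **Table 1 note, 3.7.5.3 and Table 6 (Phase 4):** state that Phase 4 effect models use only covariate values recorded before allocation, namely the visit 1 IPAQ and, where used, visit 1 body measures.
- **Table 1 note:** add that anthropometry and body composition after baseline are outcomes in Phase 4 and are not covariates there.
- **3.7.5.3, and through it 3.7.5.4:** drop the covariate label from follow-up activity, and report week 6 and week 12 physical activity descriptively by arm.

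The AIC rule can stay, applied to this restricted set of candidates. Nothing extra is collected and no visit changes. The cost is a few sentences and a possible small loss of precision compared with a time-varying activity covariate.
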